### Study Population and Recruitment

This longitudinal proof-of-concept study aims to include a total of 40 patients with acute stroke, equally distributed in a PSD (n=20) and a non-PSD group (n=20). All the patients with acute stroke will be recruited from the wards of the Neurological Department of the University Hospital Tübingen.

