In the second step, for the assessment of PSCI, a global and a domain-specific PSCI score will be defined in accordance with the guidelines of the International Society for Vascular Behavioral and Cognitive Disorders [68] and similarly to previous studies [39,69-72]. Further, the distinction between average cognitive functioning and mild, moderate, or severe cognitive impairment will be made according to the performance level on norm-referenced *z* scores, which is in line with the recommendations of multiple neuropsychological societies [73]. In detail, PSCI is a 5-level performance score. Performance level within 1 SD below or above the mean is defined as average cognitive functioning (PSCI=0). A range between 1 and 2 SDs below the mean (between third and 16th percentile) on at least 1 cognitive domain is defined as mild cognitive impairment (PSCI=1). A performance level 2 SDs below the mean (lower than the third percentile) in at least 2 domains is defined as moderate (PSCI=2), while a performance level 3 SDs below the mean (lower than the first percentile) in at least 2 cognitive domains or 2 SDs below the mean in most of the domains is defined as severe cognitive impairment (PSCI=3). Due to increased mortality in the PSD group, and to accommodate clinical realities as well as access feasibility of our study protocol, we use an intention-to-treat analysis for the primary end point. Therefore, we have added a level (PSCI=4), which reflects the death of a patient before the 3-month follow-up session. The following domains are defined: attention and information speed, executive functions, verbal memory, language, visuospatial construction, and orientation (Table 1). If a cognitive domain is represented by more than 1 test, the mean of the *z* scores will be used. We do not apply explicit weighting to individual test components when creating the composite scores for global and domain-specific poststroke cognitive function to ensure that each test within a domain contributes equally to the composite score, maintaining consistency with established neuropsychological standards. The primary endpoint will be a between-group comparison of the cognitive outcome, defined as global PSCI at a 3-month follow-up (S3). The groups will also be balanced for age and sex. Secondary outcome measures will be a between-group comparison of the domain-specific PSCI at a 3-month follow-up (S3).

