Further, multivariate linear regression models will be used to analyze multi-item prognostic or predictive tools for cognitive outcome (eg, global PSCI) at the follow-up measurement (S3) by multimodal parameters assessed during the acute phase poststroke (S1), such as NIHSS, acute treatment, and working memory performance during fMRI or fMRI connectivity measures. As some tests will be digitalized using a tablet and a digitizer pencil, new parameters representing search behavior, for example, time on surface and time in air [42,74], will be recorded and might help to differentiate between PSD and non-PSD groups or identify patients with stroke with a high delirium risk.

Missing data will be handled in the following manner. For missing data in a 2-test subdomain, we plan to use the *z* score of the other test within the same subdomain. For missing data in a single test subdomain, we plan to use a multiple imputation approach or maximum likelihood estimation.

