#### Neuroimaging Data

The preprocessing of the structural and functional data will be performed using standard routines of the Statistical Parametric Mapping software (SPM12) [75] within MATLAB [67]. In the first step, lesions are delineated on T2-weighted (fluid-attenuated inversion recovery) or T1*-weighted (T1-weighted magnetization-prepared rapid gradient-echo sequence) images. In the second step, the raw data will be preprocessed including the following steps: realignment, slice timing, coregistration, normalization, and spatial smoothing. This step includes the lesion correction during the normalization process to ensure accurate spatial alignment across subjects, using standard delineation and lesion correction methods [76-78]. In the third step, first-level analysis will be conducted using a general linear model including the following 8 task regressors: 4 regressors for each condition (ie, LE, LC, object condition, and object control condition) in the encoding phase and 4 regressors for each condition (ie, LE, LC, object condition, and object control condition) in the retrieval phase. These regressors will be modeled using a delta (stick) function for the encoding phase (to best account for phasic changes in the neural response to the target set) and a boxcar function for the retrieval phase. Besides brain activation, we also plan to analyze functional connectivity within the frontal-parietal networks or ascending reticular activating system. For the diffusion tensor imaging data, fractional anisotropy, axial or radial diffusivity, mean diffusivity, and so forth will be used to analyze differences in structural connectivity.

For the retrieval phase of the working memory task, the mean reaction time for target and nontarget probes will be calculated for all the 4 task conditions. Accuracy will be calculated for each condition as a percentage of correctly identified probes. Presentation (version 23.0; Neurobehavioral Systems, Inc) [65] will be used for calculating these performance parameters. Further analysis steps will be conducted using SPSS Statistics (version 28.0.0.0; IBM Corp) [66] and MATLAB (R2024a) [67], for example, to compare the performance parameters of the task conditions between the PSD and non-PSD group, for example, multifactor ANOVA.

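### Linear regression is planned for prognostic models of global PSCI, a 5-level ordinal score, and the number of predictors is not fixed for a sample of at most 40

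*Protocol article*

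**What the plan says.** Under Statistical Analysis, Multicomponent Neuropsychological Assessment, the protocol article states that "multivariate linear regression models will be used to analyze multi-item prognostic or predictive tools for cognitive outcome (eg, global PSCI", measured at S3. The predictors are "multimodal parameters assessed during the acute phase poststroke (S1), such as NIHSS, acute treatment, and working memory performance during fMRI or fMRI connectivity measures".

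The paragraph before it defines the outcome: "In detail, PSCI is a 5-level performance score". Level 0 is average functioning. Level 1 needs one domain between 1 and 2 SD below the norm, and level 2 needs two domains at 2 SD below. Level 3 can be reached by two routes: 3 SD below "in at least 2 cognitive domains or 2 SDs below the mean in most of the domains is defined as severe cognitive impairment (PSCI=3". For the primary end point, "we have added a level (PSCI=4), which reflects the death of a patient before the 3-month follow-up session".

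The target is 40 patients (Study Population and Recruitment). Objective 4 in the Introduction is to contribute toward protective and prognostic tools.

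**The concern.** Two features of the stated method fit badly with the data it will meet.

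- **Scale.** A linear model treats 0 to 1, 1 to 2, 2 to 3 and 3 to 4 as equal distances. The level definitions do not support this: the steps differ in the depth of deficit and in the number of domains required, and level 4 is not a cognitive performance level at all. A slope in PSCI units has no fixed meaning, and fitted values are not confined to 0-4.
- **Size.** A multi-item tool is to be estimated from at most 40 patients, with an open list of predictors. Apparent fit rises with every added parameter, whether or not that parameter predicts anything.

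The results are meant to inform prognostic tools and larger multicentre studies. An optimistic R-squared, or a coefficient that depends on the coding, could be carried into that work.

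**Working it through.** The article gives no figure for this analysis that could be reproduced. The checks below use its sample size and predictor list, plus assumptions marked as such.

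**Inputs from the article**
- Target n = 40 (Study Population and Recruitment).
- Named predictor classes: NIHSS, acute treatment, working-memory performance, fMRI connectivity. That makes four, with the last two joined by an *or*.
- Measures within the working-memory class (Neuroimaging Data): "the mean reaction time for target and nontarget probes will be calculated for all the 4 task conditions", so 2 × 4 = 8 reaction times, plus one accuracy per condition (4), up to 12 in total.
- Accrual (Results): 15 patients from June 2024 to May 2025, about 12 months, or 15/12 = 1.25 per month. Recruitment to September 2025 (16 months) gives 16 × 1.25 = 20. If it runs to December 2025, as the Abstract can be read, 19 × 1.25 = 23.75, about 24. Both are extrapolations.

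**Expected R-squared with no true association:** k/(n-1)

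| Parameters k | n=40 | n=24 | n=20 |
|---|---|---|---|
| 4 (one per named class) | 4/39 = 0.10 | 4/23 = 0.17 | 4/19 = 0.21 |
| 8 (scenario) | 8/39 = 0.21 | 8/23 = 0.35 | 8/19 = 0.42 |

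**Expected shrinkage when there is a true association.** Expected apparent R² = 1-(1-R²)(n-k-1)/(n-1), and heuristic shrinkage = 1-1/F. Substituting the first into F gives F = 1 + R²(n-1)/[(1-R²)k]. For k=4, n=40:
- assumed true R² = 0.2: F = 1 + 0.25 × 39/4 = 3.44, shrinkage 0.71
- assumed true R² = 0.3: F = 1 + 0.4286 × 39/4 = 5.18, shrinkage 0.81
- assumed true R² = 0.5: F = 1 + 1 × 39/4 = 10.75, shrinkage 0.91

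Shrinkage of 0.90 needs F = 10, so k = R²(n-1)/[9(1-R²)]. At n=40 this gives k = 1.1, 1.9 and 4.3 for true R² of 0.2, 0.3 and 0.5. Conversely, four parameters need n = 145, 85 or 37.

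**Simulation** (2000 runs, n=40, continuous outcome, assumed true R² 0.3): mean apparent R² against out-of-sample R² is 0.36 against 0.20 with 4 parameters, and 0.44 against 0.09 with 8.

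**Dependence on the death code.** Take an invented table of 20 patients per group, with counts at levels 0 to 4 of 3, 5, 5, 3, 4 (PSD) and 5, 7, 5, 2, 1 (non-PSD). With death coded 4, the means are 40/20 = 2.00 and 27/20 = 1.35, a difference of 0.65. Each unit added to the death code adds (4-1)/20 = 0.15. Codes 5, 6 and 10 therefore give 0.80, 0.95 and 1.55. The standardised difference stays between 0.51 and 0.54.

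**The case against.** Several stronger readings are tempting, and the article does not support them.

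- *Deaths will be regressed as a score of 4.* Level 4 is introduced for the primary end point. The regression sentence does not say whether deaths enter. Without them, PSCI is still ordinal.
- *The model has many predictors.* No count is given, the list is open, and more than one model is planned. The tablet-pen measures are mentioned for telling the groups apart and for delirium risk, not as predictors of PSCI. Eight parameters is a scenario.
- *No penalisation or validation is planned.* This may stand in an analysis plan that is not shown, so its absence here is not counted.
- *The fit would be largely chance.* That holds only if there is no true association. With 4 parameters and a true R² of 0.3, 0.20 of an apparent 0.36 survives out of sample. With 4 parameters and a true R² of 0.5, overfitting is mild.

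It is also fair that global PSCI is given only as an example. A linear model for a composite z score would be reasonable. In the invented table the coding of death hardly moves the standardised effect, so the harm lies in raw coefficients and predictions more than in detecting an association. The analysis is neither primary nor secondary, and the Discussion calls the study underpowered and its prognostic aim preliminary.

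That concession does not settle the point. Low power concerns missed effects, whereas overfitting inflates apparent prediction. Nothing in the Discussion addresses a linear model for an ordinal score.

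**Conclusion.** The point holds in a limited form. The mismatch between linear regression and the ordinal score it names is in the text and rests on no assumption. The overfitting part is conditional on how many parameters are used and how strong the true association is. At the full 40 patients, one parameter per named class is already more than the sample supports if true R² is 0.2-0.3 (shrinkage 0.71-0.81), and about right if it is 0.5. Lower accrual makes this worse, but n=20 and n=24 are projections. Severity is modest: the change should be made, but the primary comparison does not depend on it.

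**What to change.** - **Model.** For global PSCI, use proportional-odds (ordinal logistic) regression with deaths kept as the worst level, and say so. Set a rule beforehand for collapsing sparse adjacent levels, since five levels in 40 or fewer patients may leave thin cells.
- **Linear regression.** Keep it only for the continuous mean domain z score, labelled as a supportive analysis in survivors.
- **Predictors.** An ordinal model does not lift the limit on predictors. Prespecify about 1-2 parameters, for example S1 NIHSS and one working-memory or connectivity summary, or use a penalised fit for a larger set.
- **Reporting.** Give bootstrap optimism-corrected performance alongside apparent fit.

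The cost is a change of wording and a little more analysis work. Ordinal regression is available in SPSS, and the bootstrap or penalised fit can be done in MATLAB; both programs are already named in the article. No further data are needed, and analysis is due to start only at the beginning of 2026. The downside is a less favourable apparent fit.

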WM^d^ span within NAB Module Attention [47]	✓	✓	✓
TMT—Part B [46]	✓	✓	✓
Verbal memory			
MIS^e^ within MoCA^f^ [48]	✓	✓	✓
Language			
LIS^g^ within MoCA [48,49]	✓	✓	✓
Visuospatial construction			
VIS^h^ within MoCA [48,49]	✓	✓	✓
Orientation			
OIS^i^ within MoCA [48,49]	✓	✓	✓
Cognitive impairment			
MoCA [48]	✓	✓	✓
Questionnaires assessing cognitive functioning			
Self-rating CFQ^j^ [50]	✓		
Relative questionnaire: IQCODE^k^ [51]	✓		
Depression			
GDS^l^ [52]	✓	✓	✓
Quality of life			
SF^m^-12 [53]	✓		✓
Global disability			
(p)mRS^n^ [54]	✓		✓
Delirium screening			
ICDSC^o^ [55]	✓	✓	✓
Stroke symptoms			
NIHSS^p^ [35]	✓	✓	✓
Other variables			
Verbal intelligence test (MWT-B^q^ [56])	✓		
Demographics	✓		
Stroke location, medical interventions, comorbidities, etc	✓		

a S: session.

b TMT: trail making test.

c NAB: Neuropsychological Assessment Battery.

d WM: working memory.

e MIS: memory index scale.

f MoCA: Montreal Cognitive Assessment.

g LIS: language index scale.

h VIS: visuospatial index scale.

i OIS: orientation index scale.

j CFQ: cognitive failure questionnaire.

k IQCODE: Informant Questionnaire on Cognitive Decline in the Elderly.

l GDS: Geriatric Depression Scale.

m SF: Short Form health survey.

n (p)mRS: (pre)modified Rankin scale.

o ICDSC: Intensive Care Delirium Screening Checklist.

p NIHSS: National Institutes of Health Stroke Scale.

q MWT-B: German intelligence test *Mehrfach-Wortschatz-Intelligenztest*.

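### Maximum likelihood, offered as an equal alternative to multiple imputation for single-test domains, gives no patient z score for the PSCI cut-offs, and its fill-in form misgrades patients

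*Protocol article*

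**What the plan says.** The Statistical Analysis section (Multicomponent Neuropsychological Assessment) defines six cognitive domains and a PSCI level set by how many of a patient's domain z scores fall below cut-offs. The moderate grade, for example, reads: "A performance level 2 SDs below the mean (lower than the third percentile) in at least 2 domains is defined as moderate (PSCI=2". Mild uses the range from -1 to -2 SD in at least one domain. Severe uses -3 SD in at least two domains, or -2 SD in most of them. Death before follow-up is level 4. Global PSCI at 3 months (S3) is the primary endpoint and domain-specific PSCI the secondary.

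The same section has two missing-data rules. For domains with two tests: "For missing data in a 2-test subdomain, we plan to use the *z* score of the other test within the same subdomain". For domains with one test: "For missing data in a single test subdomain, we plan to use a multiple imputation approach or maximum likelihood estimation". It does not say which of the two methods applies to PSCI.

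Table 1 shows which domains fall under which rule. Attention and executive functions have two entries each, none from the MoCA. Verbal memory, language, visuospatial construction and orientation have one entry each, all MoCA index scores; the last three are labelled "within MoCA [48,49". The MoCA is given at all three sessions.

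**The concern.** The sentence treats two methods as interchangeable that are not so for this endpoint. PSCI needs a value for each patient that can be held against a threshold. Direct maximum likelihood uses incomplete records to estimate means, variances and regression coefficients, and leaves the missing value missing. It could give model-implied class probabilities, but the text plans none. It yields a patient value only as a fitted conditional mean, as in an EM fill-in. Such values lack the residual variance, so they cross a distant cut-off too rarely and a near one at the wrong rate.

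The layout of Table 1 concentrates the problem. One missing S3 MoCA removes four of the six domains, and two domains below -2 SD are enough for the moderate grade. The imputed domains can therefore decide the level on the primary endpoint.

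**Working it through.** The article gives no missing-data rate and no domain means or correlations, so there is no figure of its own to reproduce. Its percentiles agree with its cut-offs: Φ(-1) = 15.9%, Φ(-2) = 2.3%, Φ(-3) = 0.13%.

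**Assumptions.** Six domain z scores are jointly normal with SD 1, common mean m and common correlation r of 0.3, 0.5 or 0.7. The whole MoCA is missing; attention and executive functions are observed. Count rule as written, with *most* read as at least 4 of 6 and a single domain below -2 SD scored as mild.

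**Spread lost by the fill-in.** The conditional mean of a missing domain is m + [r/(1+r)] × (z_att + z_exec - 2m). Its variance is R² = 2r²/(1+r).
- r = 0.3: 0.18/1.3 = 0.138
- r = 0.5: 0.50/1.5 = 0.333
- r = 0.7: 0.98/1.7 = 0.576

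At r = 0.5 the filled score has SD √0.333 = 0.577 instead of 1.
- m = -1, below -2 SD: true Φ(-1) = 15.9%; filled Φ(-1/0.577) = 4.2%.
- m = -1.5, below -1 SD: true Φ(0.5) = 69.1%; filled Φ(0.5/0.577) = 80.7%. Here impairment is over-counted.

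**Global PSCI.** Simulation, 300,000 patients per setting, r = 0.5, true share then fill-in share:

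| m | PSCI ≥2 | PSCI = 3 |
|---|---|---|
| -0.5 | 9.6% / 1.9% | 2.0% / 0.5% |
| -1.0 | 24.6% / 6.9% | 7.9% / 4.2% |
| -1.5 | 47.6% / 21.1% | 21.9% / 19.3% |
| -2.0 | 71.6% / 50.2% | 44.5% / 50.2% |
| -2.5 | 88.3% / 80.6% | 69.0% / 80.6% |

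Over r = 0.3 to 0.7 at m = -1, the share at PSCI ≥2 is 23-25% true and 5-10% filled. At m = -0.5 and -1.0 the filled level equals the true level in 57-76% of patients. Mean PSCI is too low in every setting down to m = -2. At m = -2.5 it is too high for r = 0.3 (2.65 true, 2.82 filled) and r = 0.5 (2.57, 2.61), and slightly too low for r = 0.7 (2.50, 2.47). Severe is over-counted at low means because the four filled scores are identical under equal correlations and cross -2 SD together.

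**With one earlier MoCA as predictor** (same-domain r 0.75, assumed), m = -1. The filled share at PSCI ≥2 is 18-19% if correlations between different domains across sessions are 0.75r. If they equal r, it is 9.8% + 6.9% = 16.7% at r = 0.5. In that second setting 20.2% of patients are graded too low and 4.1% too high.

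**Random draws** from the conditional distribution give 14.4/60.9/16.9/7.8% for levels 0 to 3 at m = -1, r = 0.5. Complete data give 14.3/61.1/16.7/7.9%; conditional means give 33.5/59.6/2.7/4.2%. The draws used the true parameters, so this shows the principle, not the performance with 40 patients.

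**Group difference.** Two groups with assumed missing-MoCA rates (non-PSD/PSD) of 5%/10%, 10%/20% or 10%/10%, filled from the two other domains. The difference in mean PSCI as a ratio to the truth:
- m = -0.5 vs -1.0: 0.84-0.99
- m = -1.0 vs -1.5: 0.87-1.01
- m = -1.0 vs -2.0: 1.00-1.03
- m = -1.5 vs -2.5: 1.01-1.09

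With one earlier MoCA as predictor, all settings lie within 0.97-1.02.

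**Reach.** At an assumed 5-20% missing MoCA, 0.05 × 40 = 2 to 0.20 × 40 = 8 patients are affected. At m = -1, r = 0.5, about 38% of them are graded too low under fill-in from the two other domains: 0.8 to 3.0 patients.

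**The case against.** Multiple imputation is suitable and is named first. The article never mentions EM or conditional means, so the fill-in is an inference about how the second option would be made to work. Maximum likelihood is legitimate for continuous outcomes, and which method serves which analysis could be settled in an analysis plan not shown. The number of patients is small and unknown: deaths have their own level, home or rehabilitation-centre visits are offered, and the study calls itself an underpowered proof of concept.

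Most of this stands, and it limits the size of the point. It does not remove it. The published sentence permits, without restriction, a method that cannot deliver the quantity the primary endpoint is built on.

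Three stronger readings are tempting, and the documents do not support them.
- A reader might infer that the fill-in always hides impairment. It pulls toward the mean, and the calculations show over-counting at the -1 SD cut-off when the mean is below -1, and of severe grades at means of about -2 or lower.
- A reader might infer that the group difference must shrink because PSD patients have more missing tests. The ratio falls on either side of 1. The Discussion expects more dropout in PSD patients, which is not the same as a missing MoCA in a patient who attends S3.
- A reader might take the fall from 23-25% to 5-10% as the expected size. It holds only if the S1 and S2 MoCA are ignored. A patient who misses S3 entirely is a different case, not covered here.

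**Conclusion.** The point holds in a limited form. For PSCI, maximum likelihood is not an alternative to multiple imputation: directly applied it gives no score to grade, and as a conditional mean it misgrades individuals in every setting examined. The error is mostly too mild for domain means down to about -2 and can be too severe below that. At mean -1, a true 23-25% moderate or severe becomes 5-10% with the weakest predictors, and about 17-19% with one earlier MoCA. All of this rests on assumed normal, equicorrelated z scores and on a wholly missing MoCA. The effect on the primary comparison cannot be sized or signed without the missing-MoCA rate and the group means. It is probably a matter of a few patients, but there are only 20 per group and the correction is one of wording.

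**What to change.** For global and domain-specific PSCI, strike the maximum likelihood alternative. State that missing domain z scores will be multiply imputed by random draws, using the patient's S1 and S2 scores in the same domain, the other S3 domains, NIHSS and group. Derive the PSCI level within each imputed data set, then pool the group comparison. Maximum likelihood may stay for models of continuous domain z scores, if the text says so.

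The cost is a change of wording before analysis starts in 2026, plus pooling results over imputed data sets. With 40 patients the imputation model has to stay small, so its predictors should be fixed in advance.
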